## Abstract

**Background:**

Pharmacokinetic (PK) boosting is the intentional use of a drug-drug interaction to enhance systemic drug exposure. PK boosting of the anticancer drug olaparib, a CYP3A-substrate, has the potential to reduce PK variability, side effects and financial burden associated with this drug. After establishing adequate pharmacokinetic exposure with boosting in the PROACTIVE-A study, the PROACTIVE-B study is designed to evaluate non-inferiority for both efficacy and toxicity of the boosted therapy compared to the standard monotherapy of olaparib.

**Methods:**

The PROACTIVE-B study is a nationwide, multicentre, prospective, randomized, non-inferiority trial. A total of 142 patients (128 patients with BRCA+, high-grade, FIGO III/IV ovarian cancer who receive olaparib as maintenance therapy; 14 patients with other approved indications for olaparib) who start olaparib treatment in line with the drug label will be randomized between the standard monotherapy of olaparib 300 mg twice daily (BID) and the boosted therapy of olaparib 100 mg BID with cobicistat 150 mg BID. The co-primary objectives are tolerability (dose reductions due to toxicity), and efficacy (progression-free survival at 12 months) in the ovarian cancer population. Secondary objectives include health status (EQ-5D-5L), patient satisfaction (Cancer Therapy Satisfaction Questionnaire (CTSQ)), and cost effectiveness using the institute for Medical Technology Assessment (iMTA) Productivity Cost Questionnaire (iPCQ) and iMTA Medical Consumption Questionnaire (iMCQ).

**Discussion:**

PK boosting of olaparib is a potentially valuable strategy to reduce the olaparib dose and the variability in olaparib exposure with fewer side effects. Moreover, the lower costs related to the boosted therapy contribute to a durable and accessible anticancer treatment for all patients.

**Trial registration:**

The PROACTIVE study has been published at ClinicalTrials.gov under NCT05078671 on October 14, 2021 and at EudraCT under 2021-004032-28 on August 24, 2021.

## Background

1

The accessibility to novel cancer treatments is at risk due to the increasing costs of newly approved drugs in combination with the rising incidence of cancer [1,2]. Hence, serious efforts should be made to keep anticancer treatment affordable and accessible for all patients.

Poly-adenosine diphosphate ribose polymerase (PARP)-inhibitors are a family of highly effective oncolytic drugs. PARP-enzymes play a key role in the repair of single strand DNA-breaks. Inhibition of PARP causes accumulation of single strand breaks and eventually apoptosis through synthetic lethality when double strand break repair mechanisms are inadequate [3]. Olaparib is a PARP-inhibitor, initially approved for the maintenance treatment of women with platinum-sensitive relapsed, Breast Cancer gene (BRCA)-mutated, high grade serous epithelial ovarian, fallopian tube, or peritoneal cancer, following a response to platinum-based chemotherapy [4,5]. Over the last years, olaparib has also been approved for the treatment of other stages of ovarian cancer, and subtypes of breast, pancreatic and prostate cancer, with more indications currently under investigation [6,7].

Olaparib is expensive with monthly expenses of $20,000 or €6,000 [[8], [9], [10]]. The increasing number of patients eligible for treatment with PARP-inhibitors has a substantial impact on health care expenditures [8,11]. Therefore, strategies are required to limit the impact of drug costs on health care budgets while facilitating global access to new and innovative therapies [12].

We propose pharmacokinetic (PK) boosting to reduce the dose of expensive anticancer drugs while improving the safety profile and maintaining efficacy for our patients. PK boosting is the lay term for administering a non-therapeutic active strong inhibitor of a metabolic enzyme, for example cytochrome P450 3A (CYP3A), together with a therapeutic drug that is metabolized by the same enzyme. For the treatment of Human Immunodeficiency Virus (HIV)-infection, PK boosting is routinely used in millions of people worldwide for over two decades and can, therefore, be considered as a feasible and safe approach to implement in practice [13,14]. Since many oral targeted oncolytic drugs are metabolized by CYP3A iso-enzymes, boosting could be a valuable tool to reduce the dose and, thereby, costs for many more anticancer drugs [15]. PK boosting will increase the bioavailability, due to pre-systemic CYP3A-inhibition, and decrease the elimination, due to systemic CYP3A-inhibition, of drugs that are substrates of this enzyme [13]. Therefore, the dose of a boosted drug may be reduced without compromising effective exposure. Additionally, inhibition of CYP3A could lead to less PK variability since metabolic capacity is a prominent cause for variability in systemic exposure [14]. Olaparib shows a wide variability in plasma concentrations which might be reduced by CYP3A-inhibition [16]. Predictable olaparib exposure will reduce the number of patients who are either unintentionally undertreated, or overtreated, which bears the potential to reduce suboptimal responses and reduce toxicity related to high exposure [17]. Moreover, intratumoral overexpression of CYP3A has been reported as a possible detoxification or resistance mechanism in many different types of cancer, including breast and ovarian cancer compared to healthy tissue [18,19]. Theoretically, inhibition of CYP3A by the “booster agent” may lead to higher intratumoral concentrations of the drug and may subsequently result in a more effective PARP-inhibition in tumour cells [20].

Recently, the proof-of-concept PROACTIVE-A study has shown that PK boosting of olaparib is feasible. The boosted therapy of olaparib 100 mg twice daily (BID) with the potent CYP3A-inhibitor cobicistat 150 mg BID increased olaparib exposure 1.45-fold compared to the standard therapy of olaparib 300 mg BID [21]. In PROACTIVE-A, patients received the boosted therapy for one week, precluding conclusions on efficacy and longer-term tolerability.

The ongoing PROACTIVE-B study aims to investigate the efficacy and tolerability of the boosted olaparib treatment compared to the standard monotherapy with the aim to implement the boosting approach for olaparib in routine clinical practice.

## Methods

2

### Design

2.1

PROACTIVE-B is a Dutch nationwide, open-label, randomised, multicentre trial comparing boosted olaparib therapy with standard dose olaparib monotherapy in patients with solid tumours (Fig. 1). Patients will be randomised 1:1 between standard olaparib monotherapy and the boosted therapy of olaparib and cobicistat by a variable block randomisation. Randomisation will be stratified by tumour type (BRCA-mutated, high-grade, serous ovarian cancer treated with olaparib after first-line platinum-based chemotherapy, or other) and response to chemotherapy (i.e., complete, or partial response). The standard full dose of olaparib monotherapy consists of 300 mg BID. The boosted full dose of olaparib consists of 100 mg BID with cobicistat 150 mg BID. Dose reductions will be performed according to Table 1, in line with the drug label and the physician's discretion. Patients will visit the outpatient clinic at baseline, after 4, 8, 12 weeks and thereafter every three months until progression or the end of olaparib therapy, in line with standard clinical care. Patients will continue treatment until they do not longer experience clinical benefit or until the end of treatment according to the drug label and/or treatment guideline. This current protocol is approved by the Medical Research Ethics Committee Oost-Nederland and is conducted in accordance with Good Clinical Practice and the Declaration of Helsinki.

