### Endpoints and assessments

2.3

The co-primary endpoints are dose reductions due to toxicity and PFS, defined as the time from randomisation until the date of either objective radiological disease progression or combined biochemical and clinical progression or death. The reasons for dose reductions will be recorded. Objective radiological disease progression will be assessed according to the Response Evaluation Criteria in Solid Tumours (RECIST) version 1.1, or modified RECIST according to the Gynecologic Cancer Intergroup (GCIG) if there is no measurable disease at baseline [22,23]. Biochemical progression is assessed according to the GCIG criteria for CA-125 and clinical progression will be established by the treating physician [23].

For toxicity, adverse events will be scored according to the Common Terminology Criteria for Adverse Events (CTCAE) version 5.0 [24]. Patient health status and quality of life will be measured with the EuroQol 5 dimensions 5 levels questionnaire (EQ-5D-5L) version 1.1 [25]. Patient satisfaction in terms of cancer therapy will be assessed with the Cancer Therapy Satisfaction Questionnaire (CTSQ) [26]. To measure costs from the societal perspective for the cost-effectiveness analysis, the Institute for Medical Technology Assessment (iMTA) Productivity Cost Questionnaire (iPCQ) and iMTA Medical Consumption Questionnaire (iMCQ) will be used [27,28]. ctDNA levels in plasma will be measured with shallow Whole Genome Sequencing (sWGS) and/or a hybrid-capture based Next Generation Sequencing (NGS) panel, dependent on the most recent insights at time of analysis. ctDNA levels will be corrected for germline and clonal haematopoietic variants with matched peripheral blood mononuclear cells. Olaparib plasma concentrations will be measured by cross-validated liquid chromatography tandem mass-spectrometry assays [21,29,30]. Intratumoral olaparib concentrations will be assessed from optional tumour biopsies. The frequency of the above-mentioned assessments is outlined in Table 2.

**Table 2 tbl2:** Overview of measurements in PROACTIVE-B study.

	Baseline	Week 4	Week 6	Week 8	Week 12	Every 3 months	Every 6 months	At progression
Clinical evaluation	X	X		X	X	X	X	
Laboratory	X	X		X	X	X	X	
Adverse events	X	X		X	X			
Radiological evaluation	X				X		X	
ctDNA	X	X		X	X			X
Plasma olaparib PK		X		X	X			
Intratumoral olaparib PK				X				X

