### Sample size calculation

2.6

Separate sample size calculations were performed for the two primary endpoints tolerability and efficacy. The type I error of 0.05 was distributed between both outcomes.

For non-inferiority of tolerability, the non-inferiority margin for dose reductions due to toxicity was set at 24 %. With a type I error of 0.01, power of 80 %, and an incidence of dose reductions of 28 % in each group [31], 71 patients need to be randomised to each treatment group. The non-inferiority margin for tolerability of 24 % is relatively large. This has been extensively discussed with the clinicians and patient advocates experienced in the treatment with olaparib. The most prominent adverse events related to olaparib therapy are anaemia and gastro-intestinal symptoms [35]. Since patients who start olaparib are initially closely monitored, these adverse events are usually detected shortly after start of olaparib and are easily and effectively managed with dose reductions. Therefore, the clinical impact of these side effects is acceptable, and the larger non-inferiority margin of 24 % was accepted.

For non-inferiority of efficacy, the non-inferiority margin for PFS rate at twelve months was set at 15 %. With a type I error of 0.04, power of 80 %, and an estimated PFS at twelve months of 88 % in each group, 64 patients need to be randomised to each treatment group [31]. The non-inferiority margin for efficacy of 15 % was set according to the EMA guideline [36]. The margin demonstrates superiority to placebo as olaparib increased progression-free survival at 12 months by 33 % compared to placebo [31]. Moreover, the non-inferiority margin has been discussed and endorsed by clinicians and patient advocates.

Thus, the total sample size was set at 142 patients, of which 128 will receive olaparib for high-grade, BRCA-mutated ovarian cancer after response on first-line platinum-based chemotherapy.

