### Statistical analysis

2.7

An intention-to-treat, and per protocol, analysis will be performed in line with guidelines. The per-protocol analysis will be leading, but it is not expected that cross-over will take place. Proportions of patients with dose reductions due to toxicity at twelve months will be compared between both treatment arms with the Chi-square test for proportions. Additionally, a Kaplan-Meier approach will be used to compare PFS rates between both treatment arms in the efficacy population.

Linear mixed-effects models will be used to evaluate differences in patient health status and therapy satisfaction over time and between treatment arms. Descriptive statistics will be used to describe adverse events and intratumoral olaparib concentration. The association between ctDNA levels and clinical outcomes (PFS/OS) will be explored with a Cox proportional hazard model with a correction for previously defined prognostic factors [37]. Additionally, cost-effectiveness will be analysed in line with the most recent guideline for economical evaluations in healthcare by the Dutch Healthcare Institute [38]. In line with this guideline, we will adopt a societal perspective and a life time horizon to calculate the costs per quality adjusted life year (QALY) in a cost-utility analysis [38].

The patterns and extend of missing data over time and between treatment arms will be explored. As the primary endpoints are easy to assess, missing data is expected to be minimal for the primary analysis. In case of unexpected high proportions of missing data or missing data that can be classified as Missing Not At Random (MNAR), imputation methods and/or sensitivity analyses will be applied [39].

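### Scheduled visits end when olaparib ends, but the co-primary PFS runs to progression or death, so 12-month follow-up of patients who stop early needs to be stated

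*Protocol article*

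**What the plan says.** Section 2.1 (Design) has visits at baseline and at weeks 4, 8 and 12, "thereafter every three months until progression or the end of olaparib therapy, in line with standard clinical care". On treatment duration it says "Patients will continue treatment until they do not longer experience clinical benefit or until the end of treatment according to the drug label" or guideline. The visit schedule therefore has two possible ends, and one of them is the end of olaparib.

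Section 2.3 (Endpoints and assessments) has PFS "defined as the time from randomisation until the date of either objective radiological disease progression or combined biochemical and clinical progression or death". Nothing there ends the endpoint when treatment ends, and no censoring rule is given. Table 2 lists imaging at baseline, week 12 and every 6 months. It has a column for progression but none for stopping treatment or for follow-up after stopping.

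Section 2.6 (Sample size calculation) says "the non-inferiority margin for PFS rate at twelve months was set at 15" percent and continues: "With a type I error of 0.04, power of 80 %, and an estimated PFS at twelve months of 88 % in each group, 64 patients" per group.

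Section 2.7 (Statistical analysis) plans Kaplan-Meier PFS rates by arm, with ITT and per-protocol analyses and the per-protocol analysis leading. It adds: "As the primary endpoints are easy to assess, missing data is expected to be minimal for the primary analysis". Imputation or sensitivity analyses are reserved for unexpectedly high or not-at-random missingness.

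**The concern.** For a patient who stops olaparib without progression, for example because of toxicity, the stated visit schedule ends before the endpoint does. Radiological progression needs a scan, and the combined biochemical and clinical route needs CA-125 and a physician's assessment. If these are no longer scheduled, the natural result is censoring at the last assessment. Kaplan-Meier is then valid only if those who stop have the same later progression risk as those who continue.

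That is doubtful here. Section 2.6 credits olaparib with a 33-point gain in 12-month PFS over placebo, so losing the drug plausibly raises risk. Stopping could also differ by arm: the Background reports 1.45-fold higher exposure with boosting in PROACTIVE-A, and the Discussion says toxicity is related to exposure. In a non-inferiority comparison, censoring away the consequences of early stopping makes the arms look more alike. The ITT analysis in particular needs outcomes after stopping.

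**Working it through.** **Step 1. The plan's own figure.** Inputs from section 2.6: 88% in each arm, margin 0.15, alpha 0.04, power 80%.

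n = 2 × 0.88 × 0.12 × (z₀.₉₆ + z₀.₈₀)² / 0.15² = 0.2112 × (1.7507 + 0.8416)² / 0.0225 = 63.1, rounded up to 64 per arm.

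This matches the article with alpha one-sided (two-sided 0.04 would give 79). Power at 64 is 80.5%. The follow-up issue does not make this figure wrong.

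**Step 2. Hazards.**
- On drug: h = −ln(0.88)/12 = 0.01065 per month.
- After stopping: k × h. The article gives no value, so k = 1 to 5 is an assumption. A placebo-like upper anchor follows from section 2.6: 88 − 33 = 55% at 12 months, hazard −ln(0.55)/12 = 0.04982, so k = 4.7.
- Share stopping before month 12 without progression: not given; 10 to 30% is assumed. The 28% in section 2.6 refers to dose reductions and is not a stopping rate.

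Under this model a Kaplan-Meier curve censored at stopping uses only on-drug time and reads 88% in each arm, whatever happens afterwards.

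**Step 3. Stopping at a constant rate over 12 months.** With share s stopping, l = −ln(1−s)/12 and

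S(12) = exp(−12(h+l)) + ∫₀¹² l·exp(−(h+l)u)·exp(−kh(12−u)) du.

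True 12-month difference that censoring would hide (percentage points):

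| Stopping, control vs boosted | k = 1 | k = 2 | k = 3 | k = 5 |
|---|---|---|---|---|
| 10% vs 20% | 0.0 | 0.6 | 1.1 | 2.0 |
| 10% vs 30% | 0.0 | 1.2 | 2.2 | 4.1 |

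**Step 4. Early stopping, spread evenly over months 0 to 6, k = 4.7.** With d = 0.04982 − 0.01065 = 0.03917, 12-month PFS among those who stop is

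0.55 × (exp(6d) − 1)/(6d) = 0.55 × 1.127 = 0.62.

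An arm with share p stopping has true PFS 0.62p + 0.88(1−p): 85.4%, 82.8% and 80.2% for p = 10%, 20% and 30%. A 10-point difference in stopping hides 0.10 × 26 = 2.6 points, and a 20-point difference hides 5.2.

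**Step 5. Effect on the error rate.** Take a true difference exactly at the margin and b points hidden. The boosted arm then appears to have PFS 0.73 + b against 0.88. The chance of falsely declaring non-inferiority is Φ(b/SE − 1.7507), with SE = √{[0.88×0.12 + (0.73+b)(0.27−b)]/64}.
- b = 0.026: SE = 0.0673, giving about 9% instead of 4%.
- b = 0.052: SE = 0.0657, giving about 17%.
- k = 3 with early stopping (b = 0.015 and 0.031): about 6% and 10%.

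This ignores the slightly larger standard error that censoring brings.

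**Step 6. Precision.** With the asymptotic Greenwood variance and censoring at stopping, power falls from 80.5% to 79.6, 78.5, 76.2 and 73.5% when 5, 10, 20 and 30% stop in each arm.

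**The case against.** The sentence in section 2.1 is about clinic visits. It does not say that imaging stops, that outcomes are no longer recorded, or that PFS is censored at stopping. Table 2 does not restrict the 6-monthly imaging to patients on treatment, and its progression column is not tied to olaparib either. Section 2.7 plans an analysis of OS, which needs vital status beyond progression, so some data collection must outlast the visit schedule. Visits follow routine care, which may pick up later progression. This is a condensed article, and censoring rules often sit in the full protocol or SAP. Section 2.6 says side effects are readily handled by reducing the dose, which argues against 20 to 30% stopping for good. The Discussion calls an increase in adverse events uncertain.

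Most of this stands. A reader might infer that patients who stop are lost to PFS, that the comparison is informatively censored, that an ITT rate cannot be estimated, or that the visit schedule contradicts the missing-data expectation. The documents support none of these as facts: no censoring rule is stated, progression and death may still be recorded, and section 2.7 provides for sensitivity analyses.

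The mismatch itself is not answered. An end of scheduled visits is stated, it falls short of the endpoint's definition, and nothing in the article says that progression assessment continues after stopping.

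**Conclusion.** The point holds as a mismatch between a stated visit rule and the definition of a co-primary endpoint, with a risk of bias that depends on conditions the documents do not settle. Bias requires that outcomes after stopping are not collected, that stopping is linked to progression risk, and that stopping or its consequences differ by arm. It favours non-inferiority only if the boosted arm stops more; if the control arm stops more, it works against boosting. It is zero if stopping is unrelated to risk.

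Over the assumed ranges, about 0 to 5 of the 15 margin points would be hidden. The top of that range needs a 20-point difference in stopping, early stops and an immediate placebo-like hazard. That is modest against the margin, but at the margin it could raise the false non-inferiority rate from 4% to between 6% and 17% in the scenarios with k of 3 or more and early stopping. Because the article describes the study as ongoing, outcomes not collected now may be hard to recover.

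**What to change.** Reconcile sections 2.1 and 2.3 and Table 2. State that, for all randomised ovarian cancer patients, progression (imaging, CA-125 and clinical) and vital status are collected on the same schedule in both arms to at least 12 months from randomisation, whatever the olaparib status. State also that stopping olaparib is not a reason to censor in the ITT PFS analysis. Since the per-protocol analysis leads, it is sensible to say in the same place how patients who stop early are handled there. If the full protocol already provides for this, the published text only needs to agree with it.

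The cost is a few sentences of wording and abstraction of routine-care scans, CA-125 results and vital status for patients who stop early. The sample size does not change.

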**Fig. 1 fig1:**
[figure not shown]
Study design of the PROACTIVE-B study. BRCA: Breast Cancer gene; CYP3A: Cytochrome P450 3A enzymes; ECOG: Eastern Cooperative Oncology Group; PK: Pharmacokinetics; PFS: Progression-free survival.

**Table 1 tbl1:** Olaparib monotherapy and boosted therapy dose levels.

	Standard monotherapy		Boosted therapy		
	Olaparib	Dose density	Olaparib	Cobicistat	Dose density
**Standard dose**	300 mg BID	100 %	100 mg BID	150 mg BID	100 %
**1st dose reduction**	250 mg BID	83 %	150 mg OD	150 mg BID	75 %
**2nd dose reduction**	200 mg BID	67 %	100 mg OD	150 mg BID	50 %

BID: twice daily; OD: once daily.

### Objectives

2.2

The primary objective of this study is to determine if boosted olaparib therapy is non-inferior to standard monotherapy concerning both tolerability and efficacy. Tolerability will be measured by dose reductions due to toxicity. Efficacy will be measured by progression-free survival (PFS) in patients with high-grade serous BRCA-mutated ovarian cancer treated with olaparib maintenance therapy after first-line platinum-based chemotherapy.

Secondary objectives include establishing potential differences in type of toxicity, patient health status, therapy satisfaction, cost-effectiveness between treatment arms. Moreover, the predictive value of circulating tumour DNA (ctDNA) as a pharmacodynamic response marker will be evaluated. Exploratory objectives include the association between olaparib PK and toxicity and efficacy, and the association between patient characteristics and olaparib PK and efficacy. Finally, differences in intratumoral olaparib concentrations between treatment arms will be explored.

